### Intervention

The primary objective of the Devon Active Villages intervention is to improve participation in physical activity by offering people of all ages increased opportunities to experience the enjoyment of sport and physical activity. The intervention will be implemented and coordinated locally by Local Delivery Partners. Local Delivery Partners include District Authority Sports Development Teams and community-based charitable organisations, some of which manage local facilities as well as maintain and develop activity opportunities in the local area. Each Local Delivery Partner will deliver the intervention in one of the seven regions. It was necessary to have different Local Delivery Partners for each area due to the large number of villages receiving the intervention in each period, and because the villages are spread across the whole county. No one Local Delivery Partner is of sufficient size to cover the whole county. Each Local Delivery Partner is given strategic support from Active Devon as well as a clear framework and timescales around the delivery of the intervention with strong focus on generating a local needs led approach to designing the activities.

Each village will receive a ‘community engagement phase’ for twelve weeks prior to the intervention (Figure 2). During this phase, Local Delivery Partners will engage with the local people, elected member structures, schools and other community groups to carry out a local needs assessment, an assessment of the activities currently on offer, and the activities’ take-up and capacity. This will often include, but not limited to, people being directly surveyed to find out what activities they would like the Devon Active Villages programme to provide.

**Figure 2 F2:**
[figure not shown]
Data collection timeline for the Devon Active Villages Evaluation study.

The programme will then deliver twelve weeks of physical activity sessions, with each village receiving at least three different types of activities. These activity sessions will be subsidised using programme funds. Local Delivery Partners will coordinate delivery of the intervention by finding suitable activity venues, purchasing necessary equipment and hiring local experts to deliver the activities. Community volunteers will also be recruited to help run the activities and will be provided with mentoring support throughout the programme. Local Delivery Partners will advertise the Devon Active Villages activity sessions using local media (e.g., newspapers, posters, leaflets, village newsletters).

Each village will also be supported for twelve months following the intervention, when Local Delivery Partners will help the communities to sustain the intervention activities, by providing specialist support, regular mentoring for the volunteers and additional funding or equipment if necessary. Additionally, local people will be offered coaching qualifications to help the villages continue the activities independently.

### Outcome measurement

The primary analysis will compare the proportion of adults meeting recommended guidelines for the minimum level of physical activity (i.e., 150 minutes of moderate intensity physical activity per week or 75 minutes of vigorous intensity physical activity per week) between the intervention and control modes. Secondary outcomes will be social support, physical activity intentions, awareness and use of local facilities, perceived village supportiveness of physical activity, and awareness and participation in the Devon Active Villages intervention.

### Data collection

Postal questionnaires and participant information sheets will be sent out to participants at baseline (in the month prior to the first intervention period commencing) and within a week of each of the four intervention periods ending (Figure 2). The participant information sheet makes clear the voluntary nature of the study and therefore informed consent to participate in the study will be implied when participants return a completed questionnaire. If the number of completed questionnaires returned within three weeks of the initial mailing is insufficient, additional questionnaires will be sent out to new households. Participants will receive the questionnaire, a participant information sheet and a prepaid return envelope. It is possible that some individuals may receive the questionnaire on two or more occasions. In such cases, if returned, demographic variables (gender, age, height, weight) will be used to identify this wherever possible. These participants will remain in the analysis, but it will be recorded that each participant has completed the questionnaire on more than one occasion.

### Measures

#### Demographic characteristics

The survey will include questions on gender, age, height, weight, health, occupation, car ownership, children in the household, and dog ownership, based on questions from national surveys from different populations (e.g., Burton et al., [25], Craig et al., [5]).

#### Physical activity

Physical activity will be measured using the short version of the International Physical Activity Questionnaire (IPAQ) [26]. The IPAQ short-form consists of questions on the number of days and time spent on physical activity at moderate and vigorous intensity, as well as time spent walking and sitting. The mean values for each activity category will be calculated and expressed as metabolic equivalent (MET) minutes per week, and combined to categorise people into ‘low’, ‘moderate’ or ‘high’ activity classifications. The self-administered short-form IPAQ has been found to have acceptable levels of validity and reliability [26].

#### Local area

To assess perceived characteristics of the local environment a scale will be used that was initially developed for use in another United Kingdom health study. Participants are asked to rate their agreement with 12 items on factors such as aesthetics, green space, access to amenities, traffic, safety and convenience of routes. The scale has been found to have acceptable levels of test-retest reliability [27]. Questions on perceived proximity and use of different recreational facilities are also included. These items were previously found to have acceptable test-retest reliability [28].

#### Physical activity campaigns/programmes

The survey will contain questions on participants’ awareness of and participation in local physical activity campaigns. The survey will also ask about awareness of Devon Active Villages, participation in programme events, and opinions on the programme.

#### Psychosocial correlates

Participants will be asked about their intentions to be more active in the future. The survey will also ask them to rate the importance they place on physical activity on a scale from 0 (not at all) to 10 (very), as well as their physical activity confidence and the extent to which they are trying to do more activity [29]. Finally, a series of eight questions will ask participants to rate their agreement with statements about their physical activity habits, social norms, and perceived village supportiveness of activity. These questions were initially developed for use in an Australian cohort study (n = 2,485) [25].

### Sample size

To detect an increase from 25% to 30% in the percentage of people who meet guidelines for recommended physical activity levels, 10 participants need to be recruited from each of the 128 villages at each study period to achieve 80% power at the 5% significance level [30]. A recent pilot for a population study of travel behaviour in the United Kingdom achieved a response rate of 20% for a short questionnaire postal survey [31]. On this basis, 50 surveys will be sent out to each village at each stage, anticipating that we will obtain at least 10 responses per village per stage (20% response rate). This means that 6,400 surveys will be sent out at every stage with the expectation that at least 1,280 will be completed and returned. If this response rate is not achieved within three weeks of the surveys being posted, an additional five surveys will be sent out to extra households for every one survey missing (20% response rate).

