**Methods/Design:**

A stepped wedge cluster randomised trial will be used to evaluate whether *Devon Active Villages* leads to increased physical activity levels in rural communities. Community engagement will help tailor activity programmes for each village; communities will then be supported for a further twelve months. The intervention will be delivered over four periods, each lasting twelve weeks. Data collection consists of a postal survey of a random sample of adults aged 18 years and over, at baseline and after each of the four intervention periods. The questionnaire includes questions on participant demographics, physical activity behaviour, local environment characteristics, awareness of local activity programmes, and psychosocial factors. Based on detecting an increase in the proportion of people who meet physical activity guidelines (from 25% to 30%), at least ten respondents are needed from each of the 128 villages at each stage (80% power at the 5% level of significance). Anticipating a 20% response rate, 6,400 questionnaires will be sent out at each stage (i.e., 50 surveys to each village). Using data from all five periods, a comparison of study outcomes between intervention and control arms will be performed, allowing for time period (as a fixed effect) and the random effect induced by correlation of outcomes (clustering) within villages.

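### The top-up mailing is sized at the same 20% response whose failure triggers it, so one round is expected to leave villages short of 10 replies if response is well below 20%

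*Protocol article*

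**What the plan says.** The Sample size section states the target as "10 participants need to be recruited from each of the 128 villages at each study period". This number is meant "to achieve 80% power at the 5% significance level", for a rise from 25% to 30% in the proportion meeting the guidelines. The Abstract words the same target as a minimum: "at least ten respondents are needed from each of the 128 villages at each stage".

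The response assumption comes from an outside pilot for a travel-behaviour study, which "achieved a response rate of 20% for a short questionnaire postal survey". The planned mailing follows from it: "50 surveys will be sent out to each village at each stage, anticipating that we will obtain at least 10 responses per village per stage". Over all villages that makes 6,400 surveys and at least 1,280 returns per stage.

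The contingency applies when the 20% rate has not been reached three weeks after posting. In that case "an additional five surveys will be sent out to extra households for every one survey missing (20% response rate".

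The Data collection section repeats the three-week check and says that new households will be approached if returns are insufficient, without a multiplier. Neither section says whether the check is made per village or across the stage, whether the top-up is repeated, or whether first-mailing replies arriving after three weeks count.

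**The concern.** The top-up is triggered by evidence that response is below 20%, yet it is sized as if the new households will reply at 20%. If the low return reflects a truly lower rate, the second mailing falls short for the same reason as the first.

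What is at stake is the cell size on which the power statement rests. The 20% comes from a different survey, so a lower rate here cannot be ruled out.

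There is a related point of wording. Fifty surveys at 20% give 10 replies on average, not at least 10.

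**Working it through.** **Inputs from the protocol.** 50 surveys per village-stage; target 10; 5 extra surveys per missing reply; 25% to 30%; 128 villages starting the intervention in groups of 22, 36, 35 and 35 over five periods (Study design section).

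**Assumptions not in the protocol.** The true response rate r (varied), independent replies, one top-up round, no late replies, a two-sided 5% test, and the ICC (varied).

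**Step 1: the plan's own figures.** 50 × 0.20 = 10; 128 × 50 = 6,400; 6,400 × 0.20 = 1,280. All reproduce. The multiplier is 1/0.20 = 5.

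**Step 2: what one round recovers.** A village short by s replies is sent 5s surveys and should expect 5s × r replies, a share 5r of its gap: 75% at r = 15%, 60% at 12%, 50% at 10%. For example, with 5 of 50 replying and r = 10%, 25 more surveys bring 2.5 replies, for a total of 7.5.

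**Step 3: mean final count.** With X ~ Binomial(50, r), the mean is 50r + 5r × E[max(0, 10 − X)]. Villages that exceed 10 keep their surplus, so at 15% this mean is slightly higher than the figure for a village exactly at its average (7.5 + 12.5 × 0.15 = 9.4).

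| True r | Short at first mailing | Mean shortfall | Mean final count | Triggered villages reaching 10 |
|---|---|---|---|---|
| 20% | 44% | 1.12 | 10 + 1.00 × 1.12 = 11.1 | 62.5% |
| 18% | 59% | 1.66 | 9 + 0.90 × 1.66 = 10.5 | 55% |
| 15% | 79% | 2.73 | 7.5 + 0.75 × 2.73 = 9.55 | 40% |
| 12% | 93% | 4.05 | 6 + 0.60 × 4.05 = 8.43 | 22% |
| 10% | 97.5% | 5.01 | 5 + 0.50 × 5.01 = 7.51 | 12% |

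The 44% in the first row is why 10 is an average and not a minimum, even when the 20% assumption is exactly right.

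**Step 4: power.** Hussey-Hughes formula with I = 128 villages and T = 5 periods. The 22/36/35/35 pattern gives U = 301, W = 28,881 and V = 851. Total variance is 0.275 × 0.725 = 0.1994; τ² = ICC × 0.1994; σ² = (1 − ICC) × 0.1994/m for m replies per cell.

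Var = Iσ²(σ² + Tτ²) / [(IU − W)σ² + (U² + ITU − TW − IV)τ²], where IU − W = 9,647 and the last bracket is 29,908.

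At m = 10 the power is 86.7% at ICC 0, 82.3% at 0.01, 79.7% at 0.02, 76.6% at 0.05 and 76.1% at 0.10. An ICC of about 0.02 reproduces the stated 80% and is used below. With it, the standard error at m = 10 is 0.0179, and 0.05/0.0179 − 1.96 = 0.83, giving 79.7%.

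At the mean counts from step 3, power is about 83% (r = 20%), 81% (18%), 78% (15%), 73% (12%) and 69% (10%). Repeating the calculation with simulated unequal cells instead of a flat m changes these by less than half a point.

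**Step 5: sensitivity to what the text leaves open.**
- Late replies: if 80% of eventual replies arrive by three weeks, an eventual 15% gives 6.0 at the check, 20 extra surveys and 7.5 + 20 × 0.15 = 10.5 in the end. An eventual 10% gives 4.0, 30 extra surveys and 5 + 3 = 8.0.
- Repeated rounds, for a village at its average: 7.5, 9.4, 9.8, 10.0 at 15%; 5, 7.5, 8.75, 9.4 at 10%.

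**The case against.** The strongest reply is that the rule is adequate near the planned rate. A village can fall below 10 by chance when the true rate is 20%. The multiplier is then correct, and 62.5% of triggered villages reach 10. Surplus replies elsewhere are kept, so the mean is 11.1 and power is slightly above that for exactly 10 per cell. The same is true at 18%. This stands. It rules out the tempting reading that the minimum is never reached where the rule is needed.

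Nor does the share of villages below 10 measure the harm. Power follows the overall cell sizes, and at 15% the loss is under 2 points.

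Three weeks is also an interim check. Nothing excludes later replies to the first mailing or further rounds, and a condensed article may leave such fieldwork detail to a fuller protocol. This stands as a limit on the size of the effect. It does not remove the point, because the article does state the multiplier and labels it with the 20% rate.

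The wording on replies is softer than a guarantee: "anticipating that we will obtain at least 10 responses per village per stage (20% response rate" states an anticipation. That is fair, although the Abstract calls ten the number needed from each village.

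Finally, a remedy based on one village's own three-week rate would be unstable. With 3 replies from 50, it would call for 7/0.06, about 117 extra surveys. That objection is accepted and shapes the fix.

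**Conclusion.** The point holds in a limited form. The top-up reuses the response rate whose failure triggers it. If response is truly below 20%, a single round with no late replies closes only a share 5r of each triggered village's gap. The expected loss of power against 79.7% at exactly 10 per cell is under 2 points at 15% response, about 6 at 12% and about 11 at 10%. It is negligible or absent at 18 to 20%, and matters from about 12% downwards.

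These figures assume the same low rate in every village and stage, independent replies and an ICC of 0.02, none of which the protocol gives.

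A reader might infer that the trial is underpowered, or that power drops from 77% to 66%. The documents do not support either. The second figure needs 10% response throughout, one round, no late replies and an ICC of 0.05, a value at which the stated 80% is not reproduced even with 10 replies per cell. This is an inexpensive improvement to a stated contingency rule, not a flaw in the design.

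**What to change.** Change the top-up sentence in the Sample size section so that the number of extra surveys is the shortfall divided by the response observed at three weeks. Use the stage-wide rate, or a village's rate pooled over earlier stages, rather than one village's rate at a single check. At 15% this sends 6.7 surveys per missing reply and at 10% it sends 10, and the mean count is then at least 10 per village-stage. Alternatively, state that rounds repeat until 10 replies are in. From the second stage on, use earlier response to size the first mailing. Describe 10 from 50 surveys as the average expected at 20% response, here and in the Abstract.

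The cost is one rewritten sentence, minor rewording and postage. At 10% response, a village short by 5 would be sent 5/0.10 = 50 extra surveys instead of 25, or 25 more. If all 128 villages responded at 10%, that would be about 128 × 25 = 3,200 more per stage, beside the 6,400 of the first mailing. Near 20% response the added cost is close to nil.

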### Statistical analysis

For any given outcome, data collected across all five periods will be used in a single analysis comparing the intervention and control modes. Analyses will use the intention-to-treat principle, with participants analysed according to the mode their village (cluster) was in for the stage at which they provided outcome data. Random effects (“multilevel”) linear regression models estimated using maximum likelihood [32] will be fitted to compare quantitative outcomes between the intervention and control modes, specifying the village effect as random; marginal logistic regression models using Generalised Estimating Equations (GEE) with information sandwich (“robust”) estimates of standard error specifying an exchangeable correlation structure [33] will be fitted to compare binary outcomes. Both the random effects model and GEE methods allow for correlation of outcomes within the same village cluster. Under both methods, a binary predictor variable will be used to indicate intervention versus control status and period of study, gender and age will be adjusted for. All analyses will be carried out using Stata software (StataCorp. 2011. *Stata Statistical Software: Release 12.* College Station, TX: StataCorp LP).

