### Recruitment and randomisation

Of the remaining 140 villages that were not part of the pilot, twelve could not be included in the evaluation due to engagement with local community members before baseline data collection had commenced. Thus, the remaining 128 villages (clusters) were recruited and randomised to first receive the intervention in one of the four periods, stratified by region. Villages with populations of 500–2000 people formed the sampling frame for the intervention. These population boundaries were set so that villages were large enough to have local facilities suitable for physical activity, but limited in the amount of activity opportunities they offered.

Data collection for the evaluation study will focus on adults aged 18 years and over. The study will use a repeated cross-sectional design, in which a random sample of people within each cluster will be surveyed at each stage. A complete list of all households in each of the 128 study villages will be obtained using the Postcode Address File (Address List Utility, Arc en Ciel, Version 3.1 PAF Quarter 1, 2011). The order in which households are approached to participate in the survey at each stage will be randomly generated. One adult per household will be randomly selected. If there are multiple eligible adults in the household, an invitation to complete the survey will be given to the adult who has most recently had a birthday.

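### The linear models for quantitative (non-primary) outcomes carry only a village random effect and no stated robust standard errors, so their standard errors may be too small

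*Protocol article*

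**What the plan says.** The Statistical analysis section of the protocol article sets out two models. The first is a set of random effects "linear regression models estimated using maximum likelihood", which "will be fitted to compare quantitative outcomes between the intervention and control modes, specifying the village effect as random". Binary outcomes get marginal logistic regression by GEE with sandwich "estimates of standard error specifying an exchangeable correlation structure". In both, "period of study, gender and age will be adjusted for", along with a binary intervention indicator. The section adds: "Both the random effects model and GEE methods allow for correlation of outcomes within the same village cluster".

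The primary outcome (Outcome measurement) is the proportion meeting activity guidelines. It is binary and so falls under the GEE. The linear model serves only quantitative outcomes, none of which is primary.

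On people who answer at more than one stage, Data collection says: "These participants will remain in the analysis, but it will be recorded that each participant has completed the questionnaire on more than one occasion". The Statistical analysis section gives that record no role.

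**The concern.** A single village effect makes two assumptions. First, two people in a village are equally correlated whether they answered in the same stage or several stages apart. Second, the intervention does the same thing in every village.

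The article gives reason to doubt the second. Activities are tailored to each village after a local needs assessment, and delivery is by different partners in seven regions (Intervention). The first is doubtful too: stages follow successive twelve-week periods, and each stage draws a new sample.

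In a stepped wedge, much of the information on the effect comes from change over time within a village, so an error in the within-village correlation passes directly into its standard error. A sandwich variance clustered on village protects against both failures. The article assigns it to the binary outcomes and does not mention it for the quantitative ones. At stake is that some quantitative secondary outcomes are declared significant too often, with intervals that are too narrow.

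**Working it through.** The article states no figure for the quantitative model, so there is none to reproduce. Its power statement concerns the binary primary outcome and is not in dispute here.

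**Inputs from the article.** Villages first treated at periods 2, 3, 4 and 5: 22, 36, 35 and 35 (Study design). Five stages; 10 respondents per village per stage (Sample size).

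**Assumed inputs (none stated).** Within-stage ICC ρ from 0.01 to 0.10; ratio r of between-stage to within-stage correlation, 1, 0.8 or 0.5; SD ω of the village-specific effect, 0.10 or 0.20 outcome SD. Outcome variance is set to 1.

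**Method.** Work with the five stage means of each village. X_k holds five period indicators and the intervention indicator for step group k, which has n_k villages.

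- Fitted covariance: V = τ²J + (σ²/10)I.
- True covariance W: diagonal ρ + (1−ρ)/10. Off-diagonal rρ (nested) or r^|s−t| ρ (exponential decay). For varying effects, add ω² d_k d_k′, where d_k is the intervention indicator.
- τ² and σ² are the values to which maximum likelihood converges under W.
- Model variance: A⁻¹, with A = Σ n_k X_k′V⁻¹X_k.
- True variance of the same estimator: A⁻¹BA⁻¹, with B = Σ n_k X_k′V⁻¹W_kV⁻¹X_k.
- Actual type I error of a nominal 5% two-sided test: 2[1 − Φ(1.96/ratio)], where ratio = true SE / model SE.

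**One case by hand (nested, ρ = 0.10, r = 0.5).** A village has 5 × 45 = 225 same-stage pairs and 1,225 − 225 = 1,000 cross-stage pairs. The fit averages their covariances: τ² = (225 × 0.10 + 1,000 × 0.05)/1,225 = 0.0592, so σ² = 0.9408. Take the difference between two stage means in one village:

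- model variance: 2 × 0.9408/10 = 0.188
- true variance: 2 × (0.10 + 0.09 − 0.05) = 0.280
- SE ratio: √(0.280/0.188) = 1.22

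The full estimator also uses between-village information. Its model SE is 0.0419 and its true SE 0.0500, a ratio of 1.19. Then 1.96/1.194 = 1.64, and type I error is 10.1%.

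**Correlation decay, equal effects: true SE / model SE (type I error)**

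| ICC | r = 1 | nested, r = 0.8 | exponential, r = 0.8 | nested, r = 0.5 | exponential, r = 0.5 |
|---|---|---|---|---|---|
| 0.01 | 1.000 (5.0%) | 1.006 (5.1%) | 1.015 (5.3%) | 1.016 (5.4%) | 1.027 (5.6%) |
| 0.02 | 1.000 (5.0%) | 1.014 (5.3%) | 1.029 (5.7%) | 1.033 (5.8%) | 1.054 (6.3%) |
| 0.05 | 1.000 (5.0%) | 1.039 (5.9%) | 1.070 (6.7%) | 1.091 (7.2%) | 1.134 (8.4%) |
| 0.10 | 1.000 (5.0%) | 1.087 (7.1%) | 1.137 (8.5%) | 1.194 (10.1%) | 1.265 (12.1%) |

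**Varying effects, no decay.** Over ICC 0.01 to 0.10, ω = 0.10 gives 1.022 to 1.026 (5.5% to 5.6%), and ω = 0.20 gives 1.083 to 1.093 (7.0% to 7.3%).

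**Repeat responders alone.** With 1% to 10% overlap between stages and a within-person correlation of 0.5 to 0.8 (both assumed), over ICC 0.01 to 0.05, the ratio is 0.967 to 0.998 (4.3% to 5.0%). Repeats raise the between-stage correlation, which pushes the opposite way from decay.

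**All three together** (exponential decay with r = 0.8, ω = 0.10, 5% overlap, person correlation 0.7): 1.04, 1.08 and 1.14 at ICC 0.02, 0.05 and 0.10 (6.0%, 6.9% and 8.7%).

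**The case against.** The strongest reply is that a random village effect with fixed period effects is a recognised stepped-wedge model, and that a condensed article need not state the variance estimator of every model. That the standard errors are model-based is indeed an inference, drawn from robust errors being named for one class of outcome and not the other. This stands as a caution. It does not remove the point, because the article does fix the random structure, and a fuller plan that followed it as written would have no protection.

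A second reply is about size: every ICC, decay and effect SD is assumed, and at ICC 0.01 to 0.02 with r = 0.8 the error is at most 3%. That also stands. A higher ICC is plausible mainly for an item such as perceived village supportiveness, where neighbours rate the same village. The article does not say which secondary outcomes will be analysed as quantitative, and awareness and participation are naturally binary.

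Two stronger readings are tempting. A reader might infer that the trial's error bars are simply wrong. The documents do not support this: the model is exact when its assumptions hold, and the primary outcome already has robust errors. A reader might also infer, from the retained repeat responders and from the statement "The order in which households are approached to participate in the survey at each stage will be randomly generated", that repeats make the standard errors too small. The calculation shows the reverse: ignoring repeats is slightly conservative.

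**Conclusion.** The point holds as a conditional weakness limited to quantitative, non-primary outcomes. If within-village correlation is weaker across stages than within a stage, or if the tailored programme works differently in different villages, the standard errors of the linear models as described are too small. The understatement is a few per cent at low ICC and substantial only when a high ICC meets marked decay. Repeat responders offset part of it and do not remove it in the combined scenarios tried. The conclusion rests on reading the linear-model standard errors as model-based, on full cells of 10, and on the assumed correlations. It has no bearing on the primary analysis.

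**What to change.** State that the linear models for quantitative outcomes will report robust standard errors clustered on village. Alternatively, fit those outcomes with the GEE and sandwich variance already planned for binary outcomes, using an identity link. Either is a one-line change, and 128 clusters are ample for the sandwich estimator. The cost is slightly wider intervals for secondary outcomes. No change to household sampling or to the identification of repeat responders is needed on this account, since neither causes standard errors that are too small.

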## Methods/Design

### Study design

The *Devon Active Villages Evaluation* (DAVE) protocol is based on a stepped wedge cluster randomised controlled trial design (Figure 1). During the DAVE study, the intervention will be rolled out sequentially to 128 rural villages (clusters) over four time periods. The evaluation will consist of data collection at five fixed time points (baseline and following each of the four intervention periods). The period in which the villages first receive the intervention will be randomly assigned, stratified by the seven regions of the county of Devon (see below). The intervention will be fully implemented by the end of the trial, with all 128 villages receiving the intervention: 22 first receiving the intervention at period 2, 36 at period 3, 35 at period 4, and 35 at period 5.

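### Crossover period is randomised within seven regions, but the stated adjustment set for both outcome models omits region, so reported standard errors tend to be slightly too wide

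*Protocol article*

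**What the plan says.** The Study design section states: "The period in which the villages first receive the intervention will be randomly assigned, stratified by the seven regions of the county of Devon". Recruitment and randomisation repeats it for the 128 villages, which were "randomised to first receive the intervention in one of the four periods, stratified by region". Region is the only stratification factor named.

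The Statistical analysis section defines two models. Quantitative outcomes get a random-effects linear model "specifying the village effect as random". Binary outcomes, which include the primary outcome, get "marginal logistic regression models using Generalised Estimating Equations (GEE) with information sandwich" standard errors and an exchangeable correlation structure. One sentence fixes the predictors for both: "a binary predictor variable will be used to indicate intervention versus control status and period of study, gender and age will be adjusted for". The abstract's account agrees, "allowing for time period (as a fixed effect) and the random effect induced by correlation of outcomes (clustering) within villages", and does not mention region either.

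**The concern.** When randomisation is restricted by a factor, that factor normally belongs in the analysis. Stratifying by region balances the regions across the four crossover waves. The effect estimate therefore varies less over possible allocations than it would under unrestricted randomisation. A model without region does not know this. It treats stable differences between regions as unexplained differences between villages and carries them into the standard error, so the reported uncertainty tends to be slightly larger than the true uncertainty.

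The article names its covariates. It includes gender and age, which played no part in the allocation, and leaves out the one factor that did. At stake are a close match between analysis and randomisation, a small amount of nominal power in a trial sized for 80%, and a choice about region that is better fixed before the data are seen.

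**Working it through.** **Inputs from the protocol article.** Waves of 22, 36, 35 and 35 villages (I = 128) and T = 5 data collection points (Study design); m = 10 respondents per village per period, 25% versus 30%, 80% power, 5% level (Sample size).

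**Assumptions.** Two-sided test; total variance at the mean proportion, 0.275 × 0.725 = 0.1994; ICC from 0.02 to 0.05; region explaining 20% to 40% of the between-village variance. The article gives none of these.

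**Formula.** Hussey-Hughes variance of the intervention effect, with s² = within-village variance / m and τ² = between-village variance:

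Var = I·s²·(s² + T·τ²) / [(I·U − W)·s² + (U² + I·T·U − T·W − I·V)·τ²]

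- U (intervention village-periods) = 22×4 + 36×3 + 35×2 + 35×1 = 301
- W (squared period totals) = 22² + 58² + 93² + 128² = 28,881
- V (squared village totals) = 22×16 + 36×9 + 35×4 + 35×1 = 851
- I·U − W = 9,647, and the coefficient of τ² is 29,908

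**The plan's own figure.** The stated 80% cannot be reproduced from the article alone, because no ICC is given. At an assumed ICC of 0.02, τ² = 0.02 × 0.1994 = 0.00399 and s² = 0.98 × 0.1994 / 10 = 0.01954. Then Var = 128 × 0.01954 × (0.01954 + 5 × 0.00399) / (9,647 × 0.01954 + 29,908 × 0.00399) = 0.000321, so SE = 0.01791. Power = Φ(0.05/0.01791 − 1.96) = 79.7%, close to the stated value.

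**Effect of adding region.** Multiply τ² by 0.8 or 0.6 and recompute:

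| ICC | Region share | SE | SE reduction | Power |
|---|---|---|---|---|
| 0.02 | none | 0.01791 | – | 79.7% |
| 0.02 | 20% | 0.01768 | 1.3% | 80.7% |
| 0.02 | 40% | 0.01741 | 2.8% | 81.9% |
| 0.05 | none | 0.01862 | – | 76.6% |
| 0.05 | 20% | 0.01840 | 1.2% | 77.6% |
| 0.05 | 40% | 0.01810 | 2.8% | 78.9% |

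Over a wider range (ICC 0.01 to 0.20, region share 10% to 50%) the SE falls by 0.2% to 4.0% and power rises by about 0.2 to 3.2 points.

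**How much of this is real precision.** The table gives the change in the model-based SE. It does not show how far the estimator's true spread changes when allocation is already stratified. A paired simulation of 3,000 replicates (linear stepped-wedge model, stratified allocation, assumed region sizes) put the fall in true spread at only about 0.2% to 1.6%. The rest of the SE change is the reported figure moving closer to the spread that the design already has.

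**Check on the logistic GEE.** In a smaller paired simulation (120 replicates per scenario, log-odds scale), adding region lowered the mean robust SE from 0.0888 to 0.0873 (ICC 0.02, share 25%) and from 0.0934 to 0.0920 (ICC 0.05, share 50%), about 1.5% to 2%. The empirical spread did not fall (0.0895 to 0.0904; 0.1049 to 0.1085). Monte Carlo error on each spread is about 6%, so this neither confirms nor excludes a true gain of 1% to 3%.

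**The case against.** The best defence is that the analysis handles the features on which a stepped wedge trial's validity depends: period, correlation within villages, and the mode each village was in at each stage. Region is a fixed attribute of a village, so stable regional differences already sit in the village random effect or the exchangeable correlation, and much of the contrast is within village. Stratified allocation keeps region nearly balanced across waves, so omitting it does not bias the effect, and an SE that is slightly too wide errs on the cautious side. All of this stands, and it limits the point to one of alignment and small precision. It does not explain why the stratifier was left out.

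A reader might infer more than the article supports in four ways:

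- *That the analysis ignores the design.* It does not. Only the stratification goes unused.
- *That the whole fall in SE is lost precision.* Most of the gain has already come from the stratified allocation.
- *That uneven waves leave a material regional imbalance.* Divisibility by seven is not the test (35 = 7 × 5); balance means proportional to each region's number of villages, which the article does not give. Exact proportionality is unattainable: 22/128 = 11/64 would require every region's count to be a multiple of 64. What remains is of rounding size, and no consequence can be calculated.
- *That regional delivery is a reason for the term.* The Intervention section says "Each Local Delivery Partner will deliver the intervention in one of the seven regions", but differences between partners would be differences in the intervention effect. A region main effect addresses neither those nor regional time trends.

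It could also be said that a journal article condenses a fuller plan. That would excuse silence about covariates, but here the list is written out.

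**Conclusion.** The point holds in a narrow form. The article randomises within regions and then states an adjustment set, for both models, that omits region. The reported standard errors therefore tend to be slightly too wide for the stratified design. Under an assumed ICC of 0.02 to 0.05 and a region share of 20% to 40%, the model-based SE is about 1% to 3% larger than it need be and nominal power about 1 to 2 points lower; the true loss of precision is about 0% to 2%. There is no bias and no sign of an inflated false-positive rate. Confidence is high that region is omitted. It is only moderate for the size, which depends on an ICC, a region share and region sizes that the article does not give. The change is worth making because it costs almost nothing.

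**What to change.** In the Statistical analysis section, add region to the adjustment list beside period of study, gender and age. State that it enters as a fixed effect (six indicator variables) in both the GEE logistic model and the random-effects linear models. Make the abstract's summary of the analysis consistent.

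The cost is one phrase and six parameters against 128 villages. Each village's region is already known from the randomisation, so no data collection changes. In the logistic model the odds ratio becomes conditional on region, as it already is on age and gender. Under the assumptions used here region accounts for at most 0.40 × 0.05 = 2% of total variance, so that shift should be slight. If the investigators also want to examine partner-specific effects or regional time trends, those need separate interaction terms.
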